## Abstract

**Background:**

Since 2004, a national Disease Management Program (DMP) has been implemented in Germany, which includes educational measures aimed at patients with type-2 diabetes (T2D). However, about 15-20% of T2D patients remain in poor metabolic control. Qualitative research shows that one reason for this might be an increasing frustration of general practitioners (GPs) with the management of their poorly regulated T2D patients over time. We aim at approaching this problem by improving the GP-patient-communication and fostering shared decision-making.

**Methods/Design:**

An educative intervention will be tested within a multi-centred cluster-randomized controlled trial (RCT) in Germany. We include 20 GPs in three regions. Each of the 60 GPs will recruit about 13 patients meeting the inclusion criteria (total of 780 patients). GPs allocated to the intervention group will receive a peer-visit from a specifically trained GP-colleague who will motivate them to apply patient-centred communication techniques including patient-centred decision aids. GPs allocated to the control group will not take part in any intervention program, but will provide care as usual to their patients. The primary inclusion criterion for patients at the time of the recruitment is an HbA1c-level of over 8.0. Primary outcome is the change of HbA1c at 6, 12, 18, and 24 months compared to HbA1c at baseline. Secondary outcomes include patient’s participation in the process of shared decision-making and quality of life.

**Discussion:**

If this intervention proves to be effective it may be integrated into the existing Disease Management Program for T2D in Germany.

## Background

In 2004, a national Disease Management Program (DMP) was implemented in Germany. This also includes educational aspects for patients with type-2 diabetes (T2D). However, we know that 15–20% of T2D patients remain in poor metabolic control in terms of their HbA1c level [1]. Poorly regulated HbA1c values are a risk factor for the development of complications like diabetic foot-syndrome, retinopathy, or cardiovascular diseases [2].

Socio-demographical and clinical characteristics alone (e. g. social situation, duration of disease) cannot explain why some T2D patients remain in poor metabolic control. Furthermore, a number of psychosocial factors can influence the quality of blood sugar regulation. These include self-efficacy, personality traits, different coping strategies, various dimensions of stress and social support as well as the relationship to the GP. Also, a flagging involvement of the physician in managing his/her patients has been discussed as another possible reason for constantly poor metabolic control [3-27].

The relationship to and the communication with the GP in the conversation can influence health parameters in general [28]. As Alazri and Neal found, there is a correlation between a higher satisfaction with the GP and better blood sugar values [29].

Interventions focussing on knowledge transfer and understanding the pathophysiology of diabetes seem to have only little impact (e.g. in terms of reaching therapeutic goals) on T2D patients (especially for the non-compliant group) [30,31]. Interventions focussing on the doctor and his practice seem to be promising, in particular when combined with a strong patient-centeredness. Currently, few studies verify these effects on the patient-level (e. g. HbA1c) [32]. Many factors and influencing variables show contradictory effects or were explored in only a few studies with clear methodological limitations. Still, some factors seem to be relevant and promising within the framework of interventions in primary health care.

The continuity of the GP-patient-relationship [33] appears suitable for getting in contact with poorly regulated T2D patients [29]. But sometimes the decreasing involvement and interest of GPs in these patients results in conversations not addressing relevant or conflict-laden issues sufficiently [34].

As shown in the literature, reaching poorly regulated T2D patients and improving their adherence can be fostered by several factors:

a. The GP should be aware of the patient’s illness concepts and keep their significance in mind when dealing with the patient’s disease [35,36].

b. The use of a patient-centred communication behaviour [37,38] (use of evidence-based decision-aids) [39] in the consultation can help reaching the “non-compliant” and complicated patients.

c. Strengthening the perception of the patients’ self-efficacy, “What can I adopt for everyday life and how?” (e.g. good diabetes regulation) [6,7], also seems to be relevant in this context.

Systematic studies over the last 20 years have provided evidence that there is no patent remedy for “successful” interventions to change the behaviour of the GP. But it is indisputable that a successful educative intervention needs to be tailored to the target group in order to implement evidence-based guidelines and patient-centred decision-making [40-43].

Starting point of DEBATE: We know that patients with poor metabolic control and their GPs have often given up on improvement. Due to their gradually built up daily routine they do not see any new possibilities to improve poor blood sugar values [44]. Within this study we want to change the communication behaviour of GPs to foster shared decision-making combined with a lasting patient empowerment. This study’s aim is to verify whether this intervention targeting at GPs is able to:

a. Reduce the HbA1c-value of the included patients by 0,5 compared to the control group.

b. Increase the participation level of the patients in the process of shared-decision making.

## Methods/Design

### Design of the study

An educative intervention will be tested under real conditions in a primary care setting within the framework of a cluster-randomized controlled study. First the participants (GPs and their patients) are recruited and baseline data will be recorded. This is followed by the randomisation of the participating GPs into intervention- and control group. Then data will be recorded at four different measure points (6,12,18,24 months after baseline). GPs allocated to the control group will not take part in any intervention program, but will treat their patients as usual. Patients of those GPs randomized into the intervention group will receive substantial empowerment. It has to be taken into consideration that the recruitment of the GPs and their patients for the study already presents a first intervention, because of the higher attention paid to the problem, by patients and GPs.

### Recruitment

#### GPs

The responsible KV^a^ in every study area provides a list of all GPs taking part in primary care. By sending invitation letters, scientific staff in the three study centres performs different waves of recruitment consecutively until the target number is reached. Each study centre recruits 20 GPs from its catchment area for the study (total = 60).

#### Patients

A computer-generated list will be compiled/created to identify all the eligible patients per practice formally complying with the inclusion criteria. A total number of 780 patients will be needed. For GPs with more than 15 poorly regulated T2D patients on their list, a random sample will be created and the list will also be stratified by gender. Then the GPs consecutively keep inviting their eligible patients until the target number of 13 per practice is reached. Finally, the data will be transferred to the responsible study centre Table 1.

**Table 1 T1:** Inclusion and exclusion criteria

	**Inclusion criteria**	**Exclusion criteria**
On patient-side	Diabetes mellitus type 2	Severe co-morbidity with a life expectancy of less than 24 months
	HbA1c-level over 8.0 at the time of recruitment	
	Ability to give informed consent	
	Sufficient German language skills	
On GP-side	Specialist for general medicine or general practicing internist or GP with KV-admission^a^	

^a^KV-Zulassung = admission of the Association of Statutory Health Insurance Physicians/permission of the panel doctor’s association.

The GPs and patients can end their participation in the study at any time. The treatment of patients who leave the study is guaranteed.

### Sample size/power calculation

Assuming a residual standard deviation of 0.9 a case number of 2x 143 (=286) patients is required to realize a randomized study on the patient-side to show a difference in the HbA1c of 0.5 with a statistical power of 80%. Due to the design of the study (cluster-randomized study with an intervention on the GPs-side) the resulting cluster-effects according to the case number have to be taken into account. The derived factor will be 1.9 assuming an ICC of 0.1 and an average cluster-size of 10. Assuming an average dropout rate of approx. 20%, it is necessary to recruit at least 54 GPs, who treat 13 patients each in order to assure no less than 10 eligible patients per GP [45]. The recruitment of 60 practices is required assuming a practice-drop-out rate of 10%. In order to achieve the calculated sample size (n = 780 patients) the study was designed as a multi-centred study with study centres in Rostock, Düsseldorf and Witten (Institute of General Practice at Rostock University, Institute of General Practice at the Heinrich-Heine University in Düsseldorf, Institute of General Practice and Family Medicine at the University of Witten/Herdecke).

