### Statistical analysis

All analyses will be performed in the ITT-population (intention-to-treat). Instead of the patients, the GPs and their practices will be randomized into clusters. Hence, for the primary analysis, a mixed model with repeated measurements will be adapted at the HbA1c-values of the follow-up. This model includes three levels of hierarchy: GP/practice, patients in the GP’s practice, repeated measurements on the patient-side. Any unstructured covariance matrix will be allowed/admitted for the repeated measurements. First the initial value will be the covariate of the model. An additional covariate on the patient- or GP-level will already be included in the primary analysis, because maldistributions are more typical for cluster-randomized studies than for individually randomized studies. They will be selected right after the patient recruitment has been finalised - considering the baseline values, but without knowing the follow-up values. The coefficient test, comparing the baseline-adjusted final HbA1c-values between the randomized groups, will be performed within the primary analysis. We will use the direct Maximum-Likelihood as the statistical estimation procedure, which results in unbiased estimated values under the missing-at-random-assumption. Alternatively, sensitivity analyses such as last-observation-carried-forward (LOCF) and other worst-case scenarios will be determined. A difference of 0,5% (HbA1c) between the groups will be considered clinically relevant. Depending on their measurement scales the secondary endpoints will be analyzed with analogue models up to the primary endpoint.

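### The stated SD of 0.9, difference of 0.5 and 80% power give about 52 patients per arm, not the 143 on which the trial size rests

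*Protocol article*

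**What the plan says.** The Sample size/power calculation section of the protocol article first sizes a trial that randomises individual patients: "Assuming a residual standard deviation of 0.9 a case number of 2x 143 (=286) patients is required". The purpose is "to show a difference in the HbA1c of 0.5 with a statistical power of 80" per cent. No significance level appears in the section.

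The section then adjusts for clustering ("The derived factor will be 1.9 assuming an ICC of 0.1 and an average cluster-size of 10"). After that it allows for about 20% patient dropout, by recruiting 13 per practice to keep 10, and for 10% practice dropout. It arrives at 54 and then 60 practices, and 780 patients.

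The target of 0.5 is used consistently elsewhere. The aims in the Background include "Reduce the HbA1c-value of the included patients by 0,5 compared to the control group", the hypotheses under Outcome measures use 0.5, and the Statistical analysis section says "A difference of 0,5% (HbA1c) between the groups will be considered clinically relevant".

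**The concern.** With a difference of 0.5 and an SD of 0.9, the standardised difference is 0.56. A two-arm comparison of that size at 80% power needs roughly 50 patients per arm, so 143 stands out at once.

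The figure of 143 is the base of the whole calculation: 286, the design-effect step, the 54 and 60 practices and the 780 patients all come from it. If it does not follow from its inputs, the stated power of the trial is unsupported. A funder or ethics committee cannot judge whether 780 patients are justified. Nor can the data safety monitoring board, which may vote to stop on interim results, tell whether a recruitment shortfall would be harmless or serious.

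**Working it through.** **Inputs from the Sample size/power calculation section:** SD 0.9; difference 0.5; power 80%; equal arms; ICC 0.1; mean cluster size 10; patient dropout about 20%; practice dropout 10%. **Assumed:** two-sided alpha 0.05, varied below.

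**1. The later steps reproduce from 286.**
- Design effect: 1 + (10 − 1) × 0.1 = 1.9.
- 286 × 1.9 = 543.4, or about 54 clusters of 10.
- 54 / 0.9 = 60 practices; 60 × 13 = 780 patients; 13 × 0.8 = 10.4 patients kept per practice.

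So clustering and dropout are not already inside the 143.

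**2. The 143 itself does not reproduce.** With n per arm = 2 × (z₀.₉₇₅ + z₀.₈)² × (SD/difference)²:
- 2 × (1.960 + 0.842)² × (0.9/0.5)² = 2 × 7.849 × 3.24 = 50.9, so 51 per arm.
- The exact t-test gives 51.84, so 52 per arm and 104 in total.
- 143 / 52 = 2.75.

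**3. Other readings of the stated inputs (t-test, SD 0.9 and difference 0.5 unless noted).**

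| Reading | n per arm |
|---|---|
| 80% power, two-sided 10% (one-sided 5%) | 41 |
| 80% power, two-sided 5% | 52 |
| 80% power, two-sided 1% | 78 |
| 80% power, two-sided 0.1% | 114 |
| 90% power, two-sided 5% | 70 |
| 99% power, two-sided 5% | 121 |
| 80% power, two-sided 5%, SD 0.9 × √2 (unadjusted change score) | 103 |

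Reading 143 as the total (71.5 per arm) gives 91% power and contradicts the 2 × 143 in the text.

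The alpha that would make 143 right at 80% power follows from 0.5/0.9 × √(143/2) = 4.698. Then 4.698 − 0.842 = 3.856, and 2 × (1 − Φ(3.856)) ≈ 0.0001.

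**4. What does give 143.** At two-sided 5% and 80% power, the t-test with a difference of one third of an SD gives 142.25, rounded up to 143. Both 0.5 with SD 1.5 and 0.3 with SD 0.9 have that ratio.

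**5. What the planned trial would deliver.** With 54 × 10 = 540 analysed patients, the effective size is 540 / 2 / 1.9 = 142.1 per arm. Power by t-test:

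| SD | Difference | Power |
|---|---|---|
| 0.9 | 0.5 | 99.7% |
| 1.2 | 0.5 | 94% |
| 1.5 | 0.5 | 80% |
| 0.9 | 0.3 | 80% |

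Using degrees of freedom from the 54 clusters lowers the two 80% entries to 78.7%.

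**6. What the stated inputs would need.** 104 × 1.9 = 197.6, about 198 evaluable patients or 20 clusters of 10. With cluster-level degrees of freedom, 20 clusters give about 77% power and 22 give about 81%. Allowing for 10% practice dropout, 20/0.9 = 22.2 and 22/0.9 = 24.4, so 23 to 25 practices. At 13 patients each that is 299 to 325 patients, about 38% to 42% of 780.

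**The case against.** The section gives no alpha, so 52 per arm is not fully determined by the text. That is true, and the 5% level is labelled here as an assumption. The conclusion does not depend on it, because no conventional level comes near 143 at 80% power.

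A stronger point is that the source of 143 cannot be established. Neither an SD of 1.5 nor a difference of 0.3 appears anywhere in the document, and any pair with the ratio one third fits. The null hypothesis under Outcome measures is worded as a difference within 0.5; testing against that margin with a true difference of 0.8 and SD 0.9 would also give 143. This reading is hard to hold, since the sample size section speaks of showing a difference of 0.5 and the Statistical analysis section describes an ordinary test of the group coefficient. A plain slip in the 143 is also possible. So the explanations offered above are inference and not exhaustive. What stands without inference is that the SD, the difference, the power and the 143 cannot all be right.

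It can also be said that little harm follows: for a target of 0.5, power is close to 80% or higher whether the SD is 0.9 or 1.5, and no analysis changes. That is fair as far as the analysis goes. It does not settle whether the trial has no margin or a very large one, nor does it justify a sample size that its own inputs do not support.

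**Conclusion.** The point holds. As written, the base sample size is about 2.75 times what its stated inputs require, and the error carries through to 60 practices and 780 patients. The later steps are arithmetically sound; the fault lies in the first sentence of the calculation.

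The consequence depends on which figure is misreported:
- If SD 0.9 and difference 0.5 are right, power is about 99.7%, the design has 80% power for a difference of 0.30, and enrolment is about two and a half times what 80% power for 0.5 needs. A significant result could then fall below the 0.5 called clinically relevant.
- If the SD is 1.5, the sample size is right and power for 0.5 is about 80% (78.7% with cluster degrees of freedom). Losses beyond the planned dropout would then leave the trial underpowered.
- If the planned difference was 0.3, it conflicts with the 0.5 in the Background, Outcome measures and Statistical analysis sections.

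The sizes assume a two-sided 5% test, equal arms, and the plan's own ICC and cluster size. The contradiction needs only that alpha is a conventional one.

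**What to change.** Go back to the original calculation and identify the inputs used. Then correct the paragraph in one of these ways:
- If SD 1.5 was used with a difference of 0.5, state SD 1.5.
- If SD 0.9 is right, keep it and state that 143 per arm gives about 80% power for 0.3 and 99.7% for 0.5. Explain why a trial of this size is wanted when 0.5 is the target named throughout.
- If neither applies, report the inputs that were used and recompute.

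In every case, state the significance level and sidedness beside the figures, and add power for 0.5 at SDs of 0.9, 1.2 and 1.5 (99.7%, 94% and 80% at 142 effective patients per arm). This shows how much a shortfall would matter.

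Under either of the first two corrections, 60 practices and 780 patients can stay. The cost is one rewritten paragraph, with no change to enrolment or analysis.

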### Randomisation

After the baseline data collection the GPs will be randomized into intervention- and control group.

### Instruments

Further instruments will be used in both groups to measure e.g. the quality of life, the participation within the process of medical decision-making and the empowerment of the patients. The instruments which are utilized are the EQ-5D (measuring the patients health status), the PAID (focussing on the problem areas in Diabetes) the PEF-FB-9 (measuring the congruence of the consultation results and the values or the attitudes of the patients) and the internationally used PACIC-D (measuring aspects of empowerment). At the different points of measurement (T0-T4) a project assistant will contact the patients by phone to disseminate the data with the help of the listed instruments. Additionally, the shortened version of a questionnaire (BÄK questionnaire), developed within a former diabetes project, will be used at baseline (T0) and at the end (T4) of the study to measure how patients live with diabetes [46].

### Data collection/-recording/-transferring

Data collection will take place at different measure points: T0-T4 (6, 12,18 and 24 months after the baseline = T0). The intervention (peer-visit) will take place after the baseline, close to T1 (see intervention).

The following data will be collected at T0 (=baseline):

Concerning the GP: age, gender, time since the practice was established, specialist title, characteristics of the practice, the GP’s marital status and the number of his/her children.

Concerning the patient: age, gender, socio-demographic basic data (educational background, profession, income, marital status, number of children), date of the first diagnosis, pharmacotherapy, initial HbA1c-level, cardiovascular risk prognosis, quality of life (EQ-5D, PAID and BÄK questionnaire), the previous involvement in decision-making processes (PEF-FB-9 and PACIC-D).

The GPs or the GPs’ assistants will collect further details (on): the glycated haemoglobin levels (HbA1c); data needed to determine the cardiovascular risk prognosis (smoking status, familiar predisposition for coronary heart disease (CHD), blood pressure, total cholesterol, HDL cholesterol, LDL cholesterol), pharmacotherapy.

The project’s research assistants will contact the patients by phone and collect all the remaining data (incl. medication taken according to the patient), by means of standardized instruments. The collected data will be recorded in a documentation sheet before being transferred into a saved database.

The data will be collected at the following points in time Table 2:

**Table 2 T2:** Measure points for data collection

	**T0**	**T1**	**T2**	**T3**	**T4**
HbA1c	x	x	x	x	x
EQ-5D and PAID	x		x		x
PEF-FB-9, PACIC-D	x	x	x	x	x
BÄK questionnaire	x				x
Pharmacotherapy	x		x		x
Cardiovascular risk prognosis	x		x		x

### Intervention

The aim of the educative intervention is to enable the participating GPs to identify the agenda and the illness concepts of the patients suffering from poorly regulated diabetes mellitus type 2 and thereby to foster shared-decision making. The focus needs to be more on the patient’s perspective in order to move away from the routine of a more GP-focussed communication without overstraining or unsettling both GPs and patients [47]. For this purpose, a change in the GPs’ communication patterns is necessary. The educational peer-visit presents an integral part of the intervention. Practicing GPs will be specially trained before serving as a peer and doing the educational outreach visit. The peer visit is then supposed to motivate and train the GP in regard to the communicational aspects of the encounter in the GP’s practice, as described in detail in the background section. The GP will also be trained to reflect upon different aspects of the disease and its treatment together with the patient. The training concept follows the Elaboration Likelihood Model [48]. In our preliminary studies we have verified the acceptance of the visits and the positive effects the peer educational outreach visit has on doctor-patient-communication [49].

GPs allocated to intervention will be provided with a computer-based decision-aid, which specifically addresses diabetes and its relation to cardiovascular risk. It is based on the already available tool arriba [50]. The communication tool is meant to be used within the consultation to demonstrate the absolute effects of lifestyle changes and pharmacotherapy in regard to macrovascular event likelihood. [51,52]. Utilizing the decision aid may lead to a more patient-centred communication and enable patients to participate in the decision-making on life-style changes and pharmacotherapy. GPs allocated to intervention will be invited to take part in two group-training sessions to deepen the content of the educational peer visit.

### Outcome measures

Primary endpoint will be the HbA1c-level at the time of the follow-up examinations (T1 = 6 months, T2 = 12 months, T3 = 18 months, T4 = 24 months after baseline). The null hypothesis: the difference of the HbA1c-value of the intervention- and the control group is not higher or lower than 0,5; alternative hypothesis: the HbA1c-value of the intervention group differs at minimum 0,5 from the HbA1c-value of the control group.

Secondary endpoints will include the survey about patients’ quality of life (BÄK questionnaire, EQ-5D, PAID), about the patient-centeredness (PEF-FB-9 and PACIC-D), and about the participation of the patients [53-57]. Data on the calculated cardiovascular risk prognosis and prescribed drugs will also be analyzed.

